#### *Application of Treatment*

The treating clinician will identify the patient by their study ID and check that they have the appropriate ID-labelled treatment. All wound dressings should be removed, and if standard of care requires debridement of the wound, that debridement will be done prior to the application of study treatment.

A piece of sterile gauze is soaked in product, and applied to the wound for ten minutes. Other study or clinical procedures can be performed during the ten-minute period.

#### *After the Application of Treatment*

Once dressing is applied, its application should be immediately removed if:

- in the opinion of the Investigator, a participant exhibits signs or symptoms of shock or an allergic reaction; OR
- in the opinion of the Investigator, a participant exhibits any other unacceptable AE that warrant its removal; OR
- if the participant requests its removal.

When a rinse dressing is removed, it should not be reapplied, and the time and date of removal should be recorded.

#### **Accountability of Study Supplies**

All material supplied is for use only in this clinical study and should not be used for any other purpose. Used agents will be discarded by clinical staff after being removed from the ulcer.

#### **Blinding**

#### **Concomitant Treatments**

All participants will receive standard ulcer care.

Aside from treatment of the study ulcer, participants may continue to take their usual medications or other medications deemed necessary by the Investigator or other prescribing healthcare practitioner, with the exception of other investigational research agents and/or immunosuppressive agents. Investigational research agents are defined as agents that have not been granted a marketing authorisation (or equivalent) for the relevant indication in the relevant jurisdiction.

If the Investigator or other prescribing healthcare practitioner deems it necessary to use another investigational research agent, and/or an immunosuppressive agent, then the participant should be withdrawn from the study prior to commencement of the new treatment if possible.

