**2 STUDY OBJECTIVES AND OUTCOME MEASURES**

**Table 1 Study Objectives and Endpoints**

| Primary Objectives                                                                        | Primary Outcome Measures                                                                                                                                                                                                                                              |
|-------------------------------------------------------------------------------------------|-----------------------------------------------------------------------------------------------------------------------------------------------------------------------------------------------------------------------------------------------------------------------|
| To assess the safety and tolerability of PAW up to 6 weeks after initiation of treatment. | The primary safety analysis will be performed based on data collected up to 6 weeks after initiation of treatment. Assessment of safety will be based on the Incidence and severity of adverse reactions, including but not limited to skin irritation or maceration. |

| Secondary Objectives                                                              | Secondary Outcome Measures                                                                                                                                                                                                                                                                                                                                                                                                                                                         |
|-----------------------------------------------------------------------------------|------------------------------------------------------------------------------------------------------------------------------------------------------------------------------------------------------------------------------------------------------------------------------------------------------------------------------------------------------------------------------------------------------------------------------------------------------------------------------------|

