| To evaluate the efficacy of PAW, at 12 and 18 weeks after initiation of treatment | 
Efficacy analysis will be performed based on data collected up to 18 weeks after initiation of treatment. Assessment of efficacy will be based on the following outcome measures of the study ulcer:
 
 
• Days to complete ulcer healing
 
• Presence and severity of infection
 
• Changes in wound quality based on ulcer assessment
 
• Quality of Life (Cardiff Wound Impact Schedule)
 
 |

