## **Withdrawal of Participants from Study**

Participants can terminate their study participation at any time and without giving a reason, without prejudice to further treatment. Participants who discontinue from the study will be asked about the reason(s) for their discontinuation only to determine the presence of any AEs. If possible and willing, they will be seen and assessed by an Investigator and have a final study visit. AEs should be followed up until resolved or stable and determined to be chronic.

Participants who withdraw from the study prior to the final scheduled visit will have the final visit procedures conducted at the time of withdrawal, if possible. If a participant withdraws due to the need for amputation of the foot/limb with the study ulcer, they will be asked to have the final visit procedures prior to the amputation, if possible.

If a participant withdraws due to the study wound being completely healed, they should have the final visit procedures.

On withdrawal, participants will have the opportunity to request that their existing data and samples be expunged from the study, to the extent it is possible to do so.

The Principal Investigator can exclude a participant from continuing in the study. Possible reasons for discontinuing a participant may include:

- Participant withdrawal of consent
- Inability to tolerate the study treatment
- Any unacceptable AEs, in the judgement of the Principal Investigator
- Participant's non-adherence to the protocol
- The use of another investigational research agent prior to Week 6 has been deemed necessary
- Termination of the study for administrative, financial, or other reasons.

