### *Recording of Adverse Events*

All AEs that occur from the time of informed consent until the participant completes or withdraws from the study will be recorded in REDCap.

SAEs deemed possibly, probably or definitely related to study treatment occurring after the participant completes the study will also be reported to the Sponsor, or delegate, if the Investigator becomes aware of them.

It is preferable that AEs are reported as diagnoses if one is able to be made, rather than individual signs and symptoms. The AE description, onset and resolution dates, severity, causality and outcome must be recorded, as well as any actions taken.

Unless a diagnosis is made, or signs and symptoms are present, laboratory values or vital signs abnormalities should only be reported as AEs if they cause the participant to discontinue from the study, the Investigator feels it is clinically significant, or they meet a criterion for a SAE.

If an AE leads to premature discontinuation of the study, the appropriate pages of REDCap must be completed.

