### **Safety Data**

Adverse events will be coded using the Medical Dictionary for Regulatory Activities (MedDRA). For each study treatment, number of participants, percentage of participants in the treatment group and numbers of TEAEs will be tabulated by system organ class and preferred term.

The study treatment information will be listed. The actual number of dressings applied will be summarised.

For the summaries of AEs, participants who experience the same AE (in terms of the MedDRA system organ class and preferred term) more than once will only be counted once for that event in the number of participants. Categorical summaries will include the

frequency, incidences (one per participant) and percentages of events for participants and will be displayed by treatment group.

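### Starting another investigational or immunosuppressive agent takes the participant out of the study rather than only off the rinse, which ends recording of new adverse events, possibly inside the 6-week primary safety window

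*Protocol*

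**What the plan says.** Section 7, Concomitant Treatments, covers both investigational and immunosuppressive agents. If one is judged necessary, "and/or an immunosuppressive agent, then the participant should be withdrawn from the study prior to commencement of the new treatment if possible". The rule applies at any point in the study.

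Section 3, Withdrawal of Participants from Study, gives an open list of reasons for which the Principal Investigator may remove someone. The matching item is "The use of another investigational research agent prior to Week 6 has been deemed necessary". It does not mention immunosuppressants. Under the same heading, participants who leave early "will have the final visit procedures conducted at the time of withdrawal, if possible", and AEs already present are followed until they resolve or stabilise.

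Section 5, Recording of Adverse Events, sets the end of data capture: "All AEs that occur from the time of informed consent until the participant completes or withdraws from the study will be recorded in REDCap". Reporting of related serious events beyond that point is written for participants who complete the study, and depends on the Investigator learning of them.

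Table 1 of Section 2 sets the window for the primary outcome: "The primary safety analysis will be performed based on data collected up to 6 weeks after initiation of treatment". Its secondary objective is "To evaluate the efficacy of PAW, at 12 and 18 weeks after initiation of treatment". Under Safety Data in Section 9, the "percentage of participants in the treatment group and numbers of TEAEs will be tabulated" by system organ class and preferred term, each participant counting once per term.

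**The concern.** Stopping a treatment and leaving a study are different events, and for safety data the difference matters. A participant who starts another agent after some PAW exposure is still informative about delayed local reactions, infection and healing. The rule ends observation of that person instead of ending only the exposure.

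Before the last rinse, this cuts into the primary outcome of a first-in-human study. An event that is never recorded cannot be recovered by any missing-data method in the SAP. After the last rinse there is no study treatment left to stop, so the rule no longer serves to keep two agents apart. What it removes is secondary efficacy and late safety follow-up.

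The two sections also differ in the agents covered, the time limit and the force of the instruction, so staff could handle the same event in different ways.

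**Working it through.** The protocol gives no figure of its own to reproduce. The check has three parts.

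**1. Is there a way to stop the rinse and stay in?** Concomitant Treatments leads to study withdrawal. The withdrawal section leads to exclusion from the study. Criteria for Postponing or Stopping Study Treatment allows deferral with later re-entry, or withdrawal. None of the three provides for permanent discontinuation of the rinse with continued follow-up. Read with the AE recording rule, study withdrawal is therefore where capture of new AEs ends.

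**2. How many visits are given up?** The schedule in Section 4 has 10 visits, at Weeks 1, 2, 3, 4, 5, 6, 8, 10, 12 and 18, with rinses at Visits 1 to 6. (Section 3's figure of 12 visits over 6 weeks does not match this schedule and is not used.) For withdrawal just after Visit k:

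- rinse-period visits lost = 6 − k (for k up to 6)
- all visits lost = 10 − k
- net of one exit visit = 9 − k

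| Withdrawn just after | Rinse-period visits lost | All visits lost | Net of exit visit |
|---|---|---|---|
| Visit 1 | 5 | 9 | 8 |
| Visit 2 | 4 | 8 | 7 |
| Visit 3 | 3 | 7 | 6 |
| Visit 4 | 2 | 6 | 5 |
| Visit 5 | 1 | 5 | 4 |
| Visit 6 | 0 | 4 | 3 |
| Visit 7 | 0 | 3 | 2 |
| Visit 8 | 0 | 2 | 1 |
| Visit 9 | 0 | 1 | 0 |

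After the last rinse the loss is thus 1 to 4 visits, or 0 to 3 net. Efficacy Analyses in Section 9 stops at 12 weeks. On that horizon, withdrawal just after Visit 6 loses 3 efficacy visits (Visits 7, 8 and 9).

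I count visits rather than days. The schedule's day column runs 0, 7, 14, 28, 35, 42 and skips day 21. It also puts the Week 18 visit on day 168, although 18 × 7 = 126 and 168 / 7 = 24.

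**3. What can one missed event do to the table?** Take 10 participants in a group, and let x be the number of the other nine who have a given preferred term. Suppose the withdrawn participant would have had a first event of that term.

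- Kept in the denominator: (x + 1)/10 − x/10 = 1/10, an understatement of 10 percentage points.
- Dropped from the denominator: (x + 1)/10 − x/9 = 1/10 − x/90, which is 10 points at x = 0 and smaller for any larger x.

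The ceiling is 10 points for one participant and one term under either choice of analysis set.

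**The case against.** The best defence is that the rule is soft and rarely triggered. It is worded as a recommendation and qualified by possibility. The exclusion criteria already screen out recent systemic immunosuppression, recent malignancy and recent investigational agents. An exit visit is planned where possible, and existing AEs are followed. The 24-hour serious-event reporting rule states no cut-off at withdrawal, and withdrawals for reasons other than AEs may be replaced. Events after the rinse has stopped and another drug has started are also hard to attribute, and withdrawal may be meant to keep confounded efficacy data out.

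This limits the size of the problem but does not remove it. None of these provisions sets up recording of new non-serious events after exit, and skin irritation and maceration, the reactions Table 1 names, will often be non-serious. Confounded data can be flagged; unrecorded data cannot be recovered.

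A reader might infer several stronger things that the protocol does not support:

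- **The two sections contradict each other.** The withdrawal list is open and discretionary, so both can be followed. They are poorly harmonised.
- **Study withdrawal costs the scheduled swabs.** Swabs are tied to a rinse (before and after it), so stopping only the rinse would lose them too.
- **Each withdrawal shifts the results by 10 points.** That needs a new event, in a participant not already counted for that term. It is a ceiling.
- **The data-removal offer makes this worse.** The clause "On withdrawal, participants will have the opportunity to request that their existing data and samples be expunged from the study" applies to every withdrawal and needs a request from the participant. It is a separate matter.

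**Conclusion.** The concern holds as a limited weakness in a data-collection rule. Followed as written, the protocol stops recording new AEs inside the primary safety window for anyone withdrawn on this ground before the last rinse. After Visit 6 it gives up as many as 4 visits (3 net of the exit visit) without preventing any co-exposure. The visit counts assume that the Section 4 schedule is the operative one and that withdrawal comes just after a visit.

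The number of participants affected is not stated and is probably small. The effect on any one tabulated incidence is at most about 10 percentage points per missed first event, assuming about 10 per group. The change is still worth making because the outcome at risk is the primary one, the amendment is cheap, and the loss cannot be repaired at analysis.

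**What to change.** Amend Concomitant Treatments and Withdrawal of Participants from Study so that they say the same thing:

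- Starting another investigational or immunosuppressive agent before or during the rinse period stops further study rinses but not study participation.
- Starting one after the last rinse leaves the visit schedule unchanged.
- In both cases, scheduled visits and AE recording continue to the final visit unless the participant withdraws consent.
- Both sections use one agent list. Any immunosuppressant applied to or near the study ulcer stays a reason to stop the rinse. Limiting the list to systemic agents, to match exclusion criterion 4, would allow a topical agent alongside PAW and confound the local reactions under study.
- The agent, route and start date, which Data collection in Section 4 already requires, are used to flag later observations.

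The cost is a wording change in two sections, with no new visits or assessments. The downside is that some efficacy and AE data will be collected under another agent and will need that flag.

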## **8 DATA AND SAMPLE MANAGEMENT**

Data collection and entry into REDCap will be completed by authorised SA Health personnel designated by the Investigator and named on this protocol. Appropriate training and security measures will be completed with the Investigator and all authorised study site personnel prior to the study being initiated and any data being entered into the system for any study participants. Data will be stored in an identifiable format (with patient URN). Data will only be downloaded and shared with University investigators and biostatistician in de-identified format; patient URN will be marked as an identifier in REDCap and removed from data exports. Procedure dates will be date-shifted in REDCap to maintain confidentiality. Identifiable data will not be accessed by non-CALHN employees. If data need to be re-identified, they can be matched by CALHN investigator against their study ID.

REDCap is a data entry form and should not constitute the original, or source document. Source documents are all documents used by the Investigator or hospital that relate to the participant's medical history, that verify the existence of the participant, the inclusion and exclusion criteria and all records covering the participant's participation in the study. They include, but are not limited to, laboratory reports, treatment dispensing records, hospital records, participant files, etc.

All participant samples will be stored in re-identifiable format by study ID at the Basil Hetzel Institute for Translational Health Research. These samples will be owned by the University of Adelaide, and staff and students of the University will analyse samples as permitted by individual participant consent. Samples will be stored based on the logged consent options defined by the participant: until the completion of the study, or for up to 5 years to allow for other relevant studies to be performed. [name] or his delegate will be responsible for annotation of samples for storage periods, custodianship and management, and destruction of samples on schedule as biological waste.

## **9 STATISTICAL ANALYSIS**

The statistical analysis principles described below will be supplemented by a statistical analysis plan (SAP), which will be finalised before the database is locked. Any changes to the statistical plans will be described and justified in the clinical study report (CSR).

The SAP will describe procedures for accounting for missing, unused, and spurious data. This section is a summary of the planned statistical analyses of the primary and secondary endpoints.

All analyses, summaries, and listings will be performed using SAS® software (version 9.4 or higher).

The following descriptive statistics will be used as applicable to summarise the study data, unless otherwise specified:

- Continuous variables: sample size [n], mean, standard deviation [SD], median, minimum [min], and maximum [max].
- Categorical variables: frequencies and percentages.

Individual participant data will be presented in listings.

### **Sample Size Assumptions**

The sample size for this study is approximately 20 participants with DFU, with approximately 10 participants in each of the two treatment groups.

As this is a Phase 0/1 study, no formal sample size has been calculated. Ten participants per group is considered appropriate for a study of this nature.

### **Demographics and Baseline Data**

Participant enrolment and disposition will be summarised for participants enrolled into the study and in each analysis set. The number of participants prematurely discontinuing from the study, along with the reason for early discontinuation will also be summarised.

Demographic and baseline data recorded at screening and prior to dosing will be summarised for all participants.

Prior medications are those medications taken on or before the first investigational product administration. Concomitant medications are medications that are taken after the first investigational product administration. Medications taken on the same day as investigational product administration will be considered as prior and concomitant medications.

### **Efficacy Analyses**

Efficacy indicators will be summarised descriptively with incidence rates or standard descriptive methods, as appropriate.

Efficacy analysis will be based on data collected up to 12 weeks after initiation of treatment. Assessment of efficacy will be based on the following outcome measures of the study ulcer:

- Days to complete ulcer healing
- Changes in ulcer quality (e.g., infection, signs, pain) on the Monash Diabetes Foot Assessment tool

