## **6 EFFICACY ASSESSMENT**

### **Ulcer Healing Assessments**

The Investigator/nurse will inspect the study ulcer at each site visit for physical (rate of healing) characteristics.

An ulcer will be considered completely healed if there is 100% reepithelialisation of the ulcer surface with no trace of exudate or drainage, as determined by the Investigator. The date of complete healing will be recorded as the date of the first assessment of 100% reepithelialization.

Note: if a participant withdraws from the study because their study wound is completely healed, they should complete Week 24 assessments.

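### The default summary of days to healing has no place for ulcers still open at the end of follow-up, and the healing date rule does not match the healing definition

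*Protocol*

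**What the plan says.** Days to complete healing is the first-listed efficacy outcome in Table 1 (Section 2) and again under Efficacy Analyses in Section 9. The method given there is "Efficacy indicators will be summarised descriptively with incidence rates or standard descriptive methods, as appropriate".

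The opening of Section 9 states what the standard methods are: "Continuous variables: sample size [n], mean, standard deviation [SD], median, minimum [min], and maximum [max"], and "Categorical variables: frequencies and percentages". They are introduced as defaults: "The following descriptive statistics will be used as applicable to summarise the study data, unless otherwise specified". The same text calls the section a summary, promises a SAP before database lock, leaves missing data to that SAP, and requires listings of individual data.

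The horizon is stated in two ways. Efficacy Analyses says "Efficacy analysis will be based on data collected up to 12 weeks after initiation of treatment"; Table 1 uses data up to 18 weeks.

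Under Ulcer Healing Assessments (Section 6), an ulcer is completely healed when there is "100% reepithelialisation of the ulcer surface with no trace of exudate or drainage". The dating rule follows: "The date of complete healing will be recorded as the date of the first assessment of 100% reepithelialization".

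**The concern.** Days to healing is a time-to-event outcome. An ulcer that is still open at the last assessment, or whose owner leaves the study or has an amputation, has no healing date. The protocol's withdrawal section foresees such exits. An open ulcer at the end of follow-up is a censored observation rather than a missing value, and none of the continuous summaries named in Section 9 accommodates censoring. A mean, SD or maximum can then be computed only among healers, a group selected by the outcome itself. If treatment heals more ulcers without making the healers much quicker, that mean hardly moves. With about 10 participants per arm it may rest on a handful of values or on none.

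The date rule is a separate fault in the text. An ulcer that is fully covered but still draining is not healed by the definition, yet it receives a healing date. This affects any analysis of the outcome, including a censored one.

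**Working it through.** **Inputs.** The protocol states no healing rate, effect size or power calculation, so there is no planned figure to reproduce. From the document: horizons T = 84 days (12 weeks, Efficacy Analyses) and T = 126 days (18 weeks, Table 1), and about 10 participants per arm. The visit table prints day 168 against week 18, which is a separate discrepancy; 18 × 7 = 126 is used here. Assumed: constant healing rate, no dropout, and 15% to 45% of controls healed by T, with the proportion doubled on treatment.

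**Formulas.** With p the proportion healed by T, the rate is λ = −ln(1 − p)/T.

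- Mean among healers: 1/λ − T(1 − p)/p
- Restricted mean days unhealed, all participants: p/λ
- Median time to healing, all participants: ln 2/λ

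**30% v 60% at T = 84.**

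- p = 0.30: 1/λ = 84/0.3567 = 235.5. Healers' mean = 235.5 − 84 × 0.7/0.3 = 235.5 − 196.0 = 39.5 days. Restricted mean = 0.30 × 235.5 = 70.7 days.
- p = 0.60: 1/λ = 84/0.9163 = 91.7. Healers' mean = 91.7 − 84 × 0.4/0.6 = 91.7 − 56.0 = 35.7 days. Restricted mean = 0.60 × 91.7 = 55.0 days.
- Medians over all participants: 163 days (so not reached by day 84) v 64 days.

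**Range at T = 84** (differences taken before rounding).

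| Healed, control v treated | Mean among healers (days) | Shift | Restricted mean, all (days) | Shift |
|---|---|---|---|---|
| 15% v 30% | 40.9 v 39.5 | 1.4 | 77.5 v 70.7 | 6.9 |
| 20% v 40% | 40.4 v 38.4 | 2.0 | 75.3 v 65.8 | 9.5 |
| 30% v 60% | 39.5 v 35.7 | 3.8 | 70.7 v 55.0 | 15.6 |
| 40% v 80% | 38.4 v 31.2 | 7.2 | 65.8 v 41.8 | 24.0 |
| 45% v 90% | 37.8 v 27.1 | 10.7 | 63.2 v 32.8 | 30.4 |

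If the healing rate rather than the proportion is doubled, the healers-only shift is 1.1 to 4.0 days over the same control range, against 5.8 to 14.2 days for the restricted mean. At T = 126 and 30% v 60%, the healers' means are 59.3 v 53.5 days (shift 5.8) and the restricted means 106.0 v 82.5 (shift 23.5).

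**Small-sample check.** Trials of 10 per arm were simulated (40,000 per setting; Weibull shapes 1, 1.5 and 2; healing dated to the next visit, on a grid that included day 21). At 30% v 60%, among trials with a healer in each arm, the healers-only mean was equal or longer on the better treatment in about 42–43%. The observed proportion healed was higher on treatment in about 88% of all trials. At 20% v 40% these figures were about 47–48% and 77–78%, and in about 11–12% of trials at least one arm had no healer and so no mean.

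**Date rule.** The definition needs two things: full re-epithelialisation, and no exudate or drainage. The date needs only the first. Take an ulcer covered but draining at visit 4 (day 28 in the visit table) and dry at visit 5 (day 35). It is dated day 28 but meets the definition on day 35, so the date is 7 days early. An ulcer covered and still draining at its last assessment has a date without ever meeting the definition.

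**The case against.** The strongest reply is that the protocol offers more than the continuous list. Incidence rates are expressly permitted where appropriate, n is printed beside each mean, categorical outcomes get percentages, and individual listings are required. A table of the proportion healed would show 30% v 60% at once. The defaults yield to other specifications, a SAP is to follow, and censoring details are commonly settled there. A Kaplan-Meier curve without a test would still count as descriptive. A median with unhealed ulcers ranked last can be computed once more than half of an arm heals.

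Much of this stands. A reader might infer that the planned output as a whole would make doubled healing look like control. The documents do not support that, since the weakness lies in one summary, the healers-only mean and its companions. Nor does the protocol say that unhealed ulcers are excluded; this is what follows if the default is applied as written. The size also depends on an assumed healing rate, and at 40–45% control healing the shift of 7 to 11 days is not trivial.

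What remains is that the protocol is not silent on method. It names a default list unsuited to censored times and does not commit to reporting the proportion healed for this outcome. On the date rule, one can read the second sentence as shorthand for the definition just before it, but as worded the two give different dates.

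**Conclusion.** The concern holds in a limited form. If the default list is applied to days to healing without an incidence of healing, the result is a healers-only figure that can hide a treatment effect. Under a constant healing rate, a doubling of the proportion healed by day 84 moves that mean by 1.4 to 10.7 days across assumed control healing of 15% to 45%. Those healing rates are assumptions. The mismatch between the healing definition and its date rests on the text alone and needs no assumption.

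A reader might go further and infer that the decision on a next trial would be misled. The documents contain no efficacy decision rule, so that does not follow. The outcome is secondary and descriptive in a safety-led study with no formal sample size. The change should be made, but the primary objective is not affected.

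**What to change.** - **Section 9, Efficacy Analyses:** summarise days to healing in all randomised participants, by arm, with a Kaplan-Meier or cumulative-incidence estimate. The latter suits the case where amputation or death precludes healing. Give the median if reached, and the number healed over all randomised with exact 95% intervals. These intervals will be wide at this size (about 7–65% for 3/10 and 26–88% for 6/10), which is honest reporting of what 10 per arm can show.
- **Horizon:** reconcile the 12 weeks under Efficacy Analyses with the 18 weeks in Table 1, because this fixes the censoring time.
- **Section 6, Ulcer Healing Assessments:** date complete healing at the first assessment at which both stated criteria are met.

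The cost is a wording change in the protocol, matching text in the SAP, and standard SAS output. Wound status, including exudate, is already assessed at each study visit, so no new data are needed.

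### Section 9 contradicts Table 1 on the secondary efficacy analysis: a 12-week instead of an 18-week data cut, and two listed outcomes instead of four

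*Protocol*

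**What the plan says.** Protocol Section 2, Table 1 (Study Objectives and Endpoints), gives the secondary objective as "To evaluate the efficacy of PAW, at 12 and 18 weeks after initiation of treatment" and the data basis as "Efficacy analysis will be performed based on data collected up to 18 weeks after initiation of treatment". It lists four outcomes for the study ulcer: time to complete healing in days; "Presence and severity of infection"; change in wound quality; and quality of life on the Cardiff schedule.

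Protocol Section 9, Efficacy Analyses, states instead: "Efficacy analysis will be based on data collected up to 12 weeks after initiation of treatment". It introduces its outcome list with the same sentence as Table 1 but names only two items: time to healing in days, and "Changes in ulcer quality (e.g., infection, signs, pain) on the Monash Diabetes Foot Assessment tool".

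The opening of Section 9 presents the section as a summary of what is planned for the primary and secondary endpoints. A statistical analysis plan, to be finalised before database lock, is to supplement it.

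The timing of the final visit is itself stated in three ways. Section 3 and the week row of the visit schedule in Section 4 place it at week 18. The study-day row of the same schedule labels it day 168. Section 6 (Ulcer Healing Assessments) refers to Week 24 assessments for participants who leave because the ulcer has healed.

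**The concern.** Both places define the same analysis, and they differ on which data enter it and which outcomes it covers. This is not detail awaiting the analysis plan: the protocol has stated the point twice, differently.

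The time-to-healing outcome depends directly on the cut. No visit is scheduled between week 12 and the final visit, so an ulcer that closes in that interval will normally first be recorded as healed at the final visit. Table 1 counts it as healed; Section 9 counts it as unhealed. The infection, wound-quality and quality-of-life data from that visit would also stay out of the efficacy summary.

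The outcome list matters in a simpler way. A programmer working from Section 9 would find no quality-of-life item among the efficacy outcomes, and nothing asking for infection severity, although Table 1 names both as secondary outcome measures.

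**Working it through.** The protocol gives no sample size calculation, power or error rate, so there is no stated figure to reproduce. The check is a comparison of text plus calendar arithmetic.

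1. **Window.** Table 1: data to 18 weeks, with 12 and 18 weeks named as the time points. Section 9: data to 12 weeks.
   - Week 12 = 12 × 7 = day 84; week 18 = 18 × 7 = day 126.
   - Excluded: 126 − 84 = 42 days; 42/126 = 33% of the Table 1 window.

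2. **Effect of the conflicting visit label.** For weeks 8, 10 and 12 the schedule's day row equals 7 × week (56, 70, 84). For the final visit it does not: 18 × 7 = 126, whereas 168 = 24 × 7.
   - If day 168 is used, the excluded period is 168 − 84 = 84 days; 84/168 = 50%.
   - The text does not settle which timing is meant, so both shares are shown.

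3. **Outcome lists side by side.**
   - Time to healing: in both.
   - Wound or ulcer quality: in both.
   - Infection presence and severity: a separate outcome in Table 1; in Section 9 infection is only an example within ulcer quality, and severity is not named.
   - Cardiff quality of life: in Table 1; absent from the Section 9 list.
   - Count: four against two.

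4. **Scale for the healing outcome (illustration only).** The protocol gives no healing rate. Assume a proportion p18 healed by week 18 of 30%, 50% or 70%, a constant healing hazard, 20 participants, and a final visit at week 18. Then p12 = 1 − (1 − p18)^(12/18), and the number healed after the Section 9 cut is 20 × (p18 − p12).
   - p18 = 30%: p12 = 21.2%; about 1.8 participants.
   - p18 = 50%: p12 = 37.0%; about 2.6 participants.
   - p18 = 70%: p12 = 55.2%; about 3.0 participants.

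   Under these assumptions, two or three participants of 20 would change healing status according to which section is followed.

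**The case against.** The strongest reply is that Section 9 is a summary and the analysis plan will complete it. That holds for anything Section 9 leaves unsaid. It does not hold here: a supplementary document cannot agree with both 12 and 18 weeks, or with both a two-item and a four-item list. Whichever it adopts departs from one part of the protocol.

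Three further replies stand in part.
- Infection is not wholly lost. It remains an example within the Monash item, and Section 4 has signs of infection assessed at each visit. What disappears is the separately listed outcome with its severity component.
- The general descriptive statistics at the start of Section 9 apply to study data at large, so it would be too strong to say that quality of life has no analysis. It is missing from the efficacy list.
- Table 1 itself names week 12 as a time point, so a week-12 summary is expected. That does not explain stopping the data there.

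A reader might also infer that the primary outcome goes unanalysed, because Table 1 says "Assessment of safety will be based on the Incidence and severity of adverse reactions" with a 6-week limit, while the Safety Data part of Section 9 says only that "numbers of TEAEs will be tabulated by system organ class and preferred term". The documents do not support that. Section 9 is silent on relatedness, severity and the 6-week limit, but silence does not contradict Table 1, which already fixes the primary outcome. Such tables are commonly left to the analysis plan, and Section 5 requires onset date, severity and causality for every event.

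Nor do the two windows show that the more favourable one could be picked after unblinding. The efficacy analysis is descriptive, the analysis plan is due before database lock, and Section 3 restricts use of the allocation list to the end of the study or a confirmed SUSAR. Finally, the absence of the before-and-after-rinse swabs from Section 9 is no inconsistency, since Table 1 lists no swab outcome.

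**Conclusion.** The contradiction stands for the secondary efficacy analysis, on both the data window and the outcome list. Followed as written, Section 9 leaves out the final visit: 42 of 126 days (33%) if that visit is at week 18, or 84 of 168 days (50%) on the day-168 label. It also lists two outcomes where Table 1 lists four.

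These findings rest on the text and need no statistical assumption. Only the illustration of two to three participants changing healing status depends on the assumed healing proportions and constant hazard.

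The affected outcomes are secondary and summarised descriptively in a study of about 20 participants whose primary outcome is safety. No test or error rate is at stake. The harm is an efficacy analysis that the protocol does not define in one way. Severity: should-fix.

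**What to change.** - **Section 9, Efficacy Analyses:** base the analysis on data up to the final visit, summarise at Week 12 and Week 18, and list the same four outcomes as Table 1. If the shorter window or list is intended, amend Table 1 and give the reasons.
- **Final visit, in the same edit:** reconcile week 18 (Section 3 and the schedule's week row), study day 168 (the schedule's day row) and the Week 24 reference in Section 6. Until these agree, the end of the efficacy window is not fixed.
- **Secondary alignment only:** let the Section 9 safety summary refer to the Table 1 primary outcome, that is, adverse reactions by severity up to 6 weeks, using the causality and severity already recorded under Section 5. This aids clarity and does not correct a contradiction.
- **Tool name:** the ulcer assessment is called the Monash Wound Assessment in Section 4 but has a different name in Section 9; use one.

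The cost is a wording change and a few more summary tables. Whether any extra data collection is needed cannot be confirmed from the text: no infection severity scale appears in the wound assessment or swab sections, and no Cardiff time points are visible, although the schedule table may be incomplete as read. Both should be checked when the edit is made.
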